# Vibration therapy as an intervention for enhancing trochanteric hip fracture healing in elderly patients: a randomized double-blinded, placebo-controlled clinical trial

**DOI:** 10.1186/s13063-021-05844-y

**Published:** 2021-12-04

**Keywords:** Hip fractures, Vibration treatment, Osteoporosis, Trochanteric fracture, Randomized controlled trial

## Abstract

**Background:**

There are more than 300,000 hip fractures yearly in the USA with mortality rates of 20% within 1 year. The treatment of osteoporotic fractures is a major challenge as bone quality is poor, and healing is expected to delay due to the impaired healing properties with respect to bone formation, angiogenesis, and mineralization. Enhancement of osteoporotic fracture healing and function is therefore critical as a major goal in modern fracture management. Previous pre-clinical studies have shown that low-magnitude high-frequency vibration (LMHFV) accelerates osteoporotic fracture healing. The objective of this study is to investigate the effect of LMHFV on accelerating trochanteric hip fracture healing and functional recovery.

**Methods:**

This is a randomized, double-blinded, placebo-controlled clinical trial to evaluate the effect of LMHFV in accelerating trochanteric hip fracture healing. All fractures undergo cephalomedullary nail fixation. The primary outcome of this study is time to fracture healing by X-ray. Computed tomography (CT) and dual-energy X-ray absorptiometry (DXA) will also be performed. Blood circulation at the fracture site will be assessed by dynamic perfusion magnetic resonance (MR). Clinical results include functional recovery by muscle strength, timed up and go test (TUG), quality of life questionnaire (SF-36), balancing, falls, and mortality.

**Discussion:**

Previous animal studies have demonstrated LMHFV to improve both normal and osteoporotic fracture healing by accelerating callus formation and mineralization. The mechanical stimulation stimulates angiogenesis by significantly enhancing vascular volume and blood flow velocity. This is the first study to translate LMHFV to enhancing hip fracture healing clinically. Positive results would provide a huge impact in the recovery of hip fracture patients and save healthcare costs.

**Trial registration:**

Clinicaltrials.gov NCT04063891. Registered on August 21, 2019

**Supplementary Information:**

The online version contains supplementary material available at 10.1186/s13063-021-05844-y.

## Background

Hip fractures are currently ranked as the top 10 causes of disability [1]. The leading cause is due to osteoporosis and the lifetime fracture risk of osteoporotic patients reaches as high as 40% [2]. There are approximately 2.5 million osteoporotic fractures each year in the United States (US), with costs estimated at 15 billion USD in 2010 [3]. In fact, 300,000 hip fractures occur yearly in the US with mortality rates of 20% within 1 year [4]. Furthermore, in the United Kingdom (UK), approximately 80,000 hip fractures are treated yearly with direct costs of 2 billion pounds and mortality of 30% at 1 year [5]. The World Health Organization (WHO) predicts that the aging population will continue to rise over the next 25 years, and therefore, the socioeconomic burden is expected to grow rapidly.

The treatment of osteoporotic fractures is a major challenge as bone quality is poor, and healing is expected to delay due to the impaired healing properties with respect to bone formation, angiogenesis, and mineralization [6–8]. Failure to unite results in pain, weakness, reduced mobility, and surgical fixation failure, and these complications are most common in elderly patients, which can lead to serious detrimental effects to overall health status. Furthermore, due to prolonged recovery, muscle function often deteriorates as well. Enhancement of osteoporotic fracture healing and function is therefore critical as a major goal in modern fracture management.

Low-magnitude high-frequency vibration (LMHFV) is a promising biophysical intervention that provides non-invasive, systemic mechanical stimulation. Previous animal studies have demonstrated LMHFV to improve both normal and osteoporotic fracture healing by accelerating callus formation and mineralization [6, 7, 9, 10]. The mechanical stimulation stimulates angiogenesis by significantly enhancing vascular volume and blood flow velocity [7]. Further investigating into the molecular pathways, we have shown LMHFV to enhance healing from the early inflammation stage to the late phases of remodeling [7, 10–13]. For the clinically relevant animal model of metaphyseal fracture healing [14], fibrinolysis was also enhanced with LMHFV to accelerate this process [15]. Improved healing was also seen with enhanced ultrastructural and functional changes of osteocytes [16]. Clinical trials have also shown positive improvements in reaction time, movement velocity, balancing ability, and quadriceps muscle strength in healthy subjects [17], which were retained 1 year after cessation of LMHFV treatment [18].

Justified with the positive results from previous pre-clinical studies, the aim is translate the use of LMHFV to enhancing hip fracture healing in clinical patients. A randomized double-blinded, placebo-controlled clinical trial is to be conducted to assess the efficacy of LMHFV in accelerating trochanteric hip fracture healing. The primary outcome is fracture healing. The secondary outcomes are densitometry, circulation, function, pain, quality of life, falls, and mortality.

## Methods

### Study design and standardization of surgical management

This is a randomized, double-blinded, placebo-controlled clinical trial to evaluate the effect of LMHFV (VH-001 exercise platform; V-health Limited, Hong Kong) on accelerating trochanteric hip fracture healing (Fig. 1). Trochanteric hip fracture patients admitted to the Orthopaedics and Traumatology ward are recruited, which are from the Prince of Wales Hospital, affiliated with the Chinese University of Hong Kong. All patients would be screened for the inclusion and exclusion criteria to meet eligibility for the study. There are more than 400 hip fractures admitted to our unit each year. Closed reduction and cephalomedullary nail fixation (Gamma3 nail, Stryker, USA) [19] will be performed for all patients within 48 h. Orthogeriatric co-care is provided for each patient to assess and treat any medical complications before operation [20]. Prophylactic intravenous antibiotic with cefazolin 1 g is given before surgical incision and continued for 3 doses after every 8 h. Postoperatively, pressure bandage will be given until mobilization. Adequate analgesics will be given. Full weight bearing with physiotherapy is started as soon as condition allows.

**Fig. 1 Fig1:**
[figure not shown]
A flowchart of the study design. The Consolidated Standards of Reporting Trials (CONSORT) checklist is provided as Additional file 1; the Standard Protocol Items: Recommendations for Interventional Trials (SPIRIT) checklist is presented in Additional file 2

### Inclusion criteria

The inclusion criteria are as follows:
Elderly male or females aged 65 years or olderUnilateral trochanteric hip fractures (AO classification A1-A3)Due to unintentional fallFractures fixed with cephalomedullary nail (Gamma nail, Stryker)Willing and able to comply with study protocol

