### Sample size

In this study, time to radiologic healing is the primary objective. This is a well-accepted quantitative approach to evaluate fracture union, as in our previous study [21]. We expect 20% acceleration of radiologic healing time (our animal data confirms 30% acceleration [9]). A sample size of 100 will detect a significant difference using ANOVA with 80% power and 0.05 significance level (PASS 11.0, NCSS, LLC, Utah, USA). Our previous clinical trial [17] confirmed that compliance of vibration treatment was very good with normal subjects at 66% on average [17]. We conservatively increase the sample size to 120, assuming 15% dropout rate.

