### Randomization and blinding

Patients will be actively screened and recruited from the Department of Orthopaedics and Traumatology, Prince of Wales Hospital, Hospital Authority, Hong Kong, based on inclusion and exclusion criteria. According to our previously established protocol [22], a computer-generated set of random allocations are sealed in consecutively numbered opaque envelopes by an independent central technician. Once consent is obtained, the patient is randomized and assigned into either vibration or placebo group by opening the next sealed envelope by a specific staff member. Patients and investigators are fully blinded until the completion of treatment. Outcome assessors and statistician are blinded.

Patient demographics will be recorded and confirmed with the Clinical Management System (CMS), Hospital Authority, which is the central electronic database for public hospitals in Hong Kong [23]. Before signing the consent form, each patient will be explained the objectives, benefits, and risks of the study and their rights and responsibilities, as well as privacy and confidentiality information. An information sheet will also be distributed.

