### Statistics

All results will be expressed in mean ± standard deviation. Statistical analysis will be performed using SPSS (IBM, NY, USA). One-way (for between-group differences in over-time changes), two-way (for interaction effect among time and group), and group repeated measures ANOVA with post-hoc Bonferroni analysis, as well as independent/paired *t* tests will be performed. Significance level is set at *p* < 0.05 (2-tailed).

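### The primary healing-time comparison uses no baseline covariate although AO A1 to A3 fractures are enrolled; prespecified adjustment for AO class and age could gain precision at almost no cost

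*Protocol article*

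**What the plan says.** - **Inclusion criteria (protocol article).** Unilateral "trochanteric hip fractures (AO classification A1-A3") are eligible from age 65. A fracture must be classified, and age known, before a patient can enter.
- **Sample size.** The section says that "time to radiologic healing is the primary objective" and adds "We expect 20% acceleration of radiologic healing time". The calculation reads "A sample size of 100 will detect a significant difference using ANOVA with 80% power and 0.05 significance level". No mean or standard deviation is given. It then says "We conservatively increase the sample size to 120, assuming 15% dropout rate".
- **Statistics.** The tests are one-way ANOVA, described as "One-way (for between-group differences in over-time changes"), two-way ANOVA for time by group, repeated-measures ANOVA with Bonferroni post-hoc tests, and t tests. "Significance level is set at *p* < 0.05 (2-tailed"). Group and time are the only factors named.
- **Randomization and blinding.** Here "a computer-generated set of random allocations are sealed in consecutively numbered opaque envelopes", following a protocol that the team had used before. The statistician is blinded.

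**The concern.** A1, A2 and A3 fractures may heal at different speeds. If they do, part of the spread in healing times is predictable from a baseline value. One-way ANOVA or a t test counts that part as random error, so the standard error of the treatment effect is larger than it need be. The trial plans for about 51 evaluable patients per arm, so such a loss would matter.

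There is also a practical side. If the arms turn out visibly unequal in fracture class and no adjustment was prespecified, any adjustment made afterwards is post hoc and open to challenge.

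**Working it through.** **Inputs from the article.** Target 20% shorter healing time; N = 100; 80% power; two-sided 0.05; 15% dropout; 120 enrolled. Two arms; 1:1 is assumed because no ratio is stated.

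**Inputs assumed.** The share p of a slower-healing class, its healing-time gap as a fraction of the mean, and hence R², the share of healing-time variance that AO class explains.

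**1. The plan's own figures.**
- N = 100 cannot be reproduced without a mean and SD. For 50 per arm it implies a standardized difference of 0.566 (t test), so SD = 0.20/0.566 = 0.353 of the control mean.
- Dropout: 100/0.85 = 117.6, so 118; 120 is consistent. Evaluable: 120 × 0.85 = 102, or 51 per arm.

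**2. Power after adjustment, starting from the stated 80%.** Adjustment multiplies the residual variance by (1 − R²), so the noncentrality is divided by √(1 − R²). At 80% power it is 1.960 + 0.842 = 2.802.

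| R² (assumed) | Noncentrality | Power | Unadjusted N of equal precision |
|---|---|---|---|
| 0 | 2.802 | 80% | 100 |
| 0.10 | 2.802/√0.9 = 2.953 | Φ(0.993) = 84% | 100/0.9 = 111 |
| 0.20 | 2.802/√0.8 = 3.132 | Φ(1.172) = 88% | 100/0.8 = 125 |

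**3. What such an R² would require.** R² = p(1 − p) × gap²/SD². With p = 0.4 and SD² = 0.353² = 0.125:
- R² = 0.10 needs a gap of √(0.10 × 0.125/0.24) = 0.23.
- R² = 0.20 needs a gap of √(0.20 × 0.125/0.24) = 0.32.

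So one class would have to heal roughly 23% to 32% more slowly. The article neither supports nor excludes this.

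**4. Type I error and power by simulation** (50 per arm, 8,000 runs per scenario).

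| p | Gap | R² | Type I error, unadjusted | Type I error, adjusted | Power, unadjusted | Power, adjusted |
|---|---|---|---|---|---|---|
| 0.2 | 30% | 0.12 | 5.4% | 4.9% | 79.4% | 83.7% |
| 0.2 | 50% | 0.32 | 5.0% | 5.4% | 80.5% | 92.7% |
| 0.3 | 50% | 0.42 | 5.3% | 5.5% | 79.8% | 95.4% |

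The Monte Carlo standard error near 5% is √(0.05 × 0.95/8000) = 0.24 points. Both analyses hold their level; they differ in power.

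**5. How far chance imbalance can move the estimate.** The SD of the between-arm difference in share is √(2p(1 − p)/n).
- With p = 0.2 and n = 50 it is √(0.32/50) = 0.080, a 95% range of ±15.7 points.
- With a 30% gap, the shift at that limit is 0.157 × 0.30 = 4.7% of the mean, or 24% of the 20% target.
- In the most extreme case tried (p = 0.5, gap 50%), the SD is 0.100 and the 95% limit is 0.196 × 0.50 = 9.8%, or 49% of the target.
- A shift equal to the whole target has a probability below 0.01% in every case tried.

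**6. Cost if class is not prognostic.** Three classes use two degrees of freedom and age one. With 100 patients the residual degrees of freedom fall from 98 to 95.

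**The case against.** **A condensed article may leave covariates to the full protocol or analysis plan.** This has force. It disposes of any complaint about stratification: a reader might infer that randomization is unstratified, but the article cites an established protocol that is not shown, so its silence is no finding. On the analysis the article is not silent. It ties the primary outcome to ANOVA and lists the tests, with group and time as the only factors.

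**Randomization already deals with imbalance.** This is right. A reader might infer that unequal fracture classes bias the comparison or could imitate much of the target effect. Neither follows. Chance imbalance is sampling error that the unadjusted standard error already contains (step 4), and over the range tried the 95% limit of the shift stays below half the target (step 5). What remains is conditional. With a 2-SD imbalance, the test statistic under no effect has mean 2√R² and variance 1 − R², and the two-sided error is about 8% at R² = 0.10 and 12% at R² = 0.20. At 1 SD it is still about 5%. That is a reason to prespecify adjustment, not evidence of an invalid test.

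**The trial is adequately powered as it stands.** A reader might infer that power is already below 80%. The article gives no mean or SD from which to show this, and on its own premise 51 per arm gives about 81%.

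**Nothing shows that AO class is prognostic.** This stands. The common nail and closed reduction described under study design may also narrow differences between classes. The size of the gain is therefore conditional.

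**The variance formula assumes continuous healing times.** This also stands. Radiographs are taken only at 6, 12 and 26 weeks after baseline, so the figures of 84% to 88% are approximate.

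**Conclusion.** The point holds as one of efficiency. The article enrols A1 to A3 fractures and fixes an unadjusted set of tests, although usable baseline information exists. With R² of 10% to 20% assumed for AO class, the stated 80% power would become about 84% to 88%, equal to the precision of about 111 to 125 patients analysed without adjustment. The calculation takes the article's 80% at face value, treats healing time as continuous, and counts no gain from age. If AO class explains little, almost nothing is gained and almost nothing is lost. The planned tests remain valid.

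**What to change.** Add one sentence to the Statistics section, or to the analysis plan, before unblinding: the primary healing-time comparison is adjusted for AO class (A1, A2, A3) and age; the repeated-measures analyses use the same covariates; the unadjusted result is reported as a sensitivity analysis. Allocation and the envelopes stay as they are.

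The cost is that sentence and about three degrees of freedom (two for class, one for age), with no extra patients or visits. One check is needed: the article implies that each fracture is classified at entry but does not say that the individual class is stored. If it is not, it can be read blind from the baseline radiographs that the article already schedules.

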### Exclusion criteria

Exclusion criteria are as follows:
Open fractureBilateral lower limb fracturesPatient with multiple injuries affecting balance/standing on platformPathological fractures e.g., tumor, infection.History of medication or disease affecting bone metabolism such as hypo/hyperthyroidism., etc.

### Malignancy

6.Chairbound or bedbound7.Cognitive problems, e.g., severe dementia.

### Drop-out criteria

Drop-out criteria are as follows:
Refusal to participateDefault follow-upReported to be unsafe for treatment

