### Adverse event handling

Currently, there is no report of adverse event in the use of LMHFV. In case of unusual conditions including intolerable pain, LMHFV treatment will be terminated and clinicians will follow-up the patient. Any adverse events or problems during the study will be verified and documented by independent staff members.

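### The drop-out criteria turn stopping treatment for safety into leaving the study, at odds with the adverse-event section and with no need to lose the X-ray outcome

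*Protocol article*

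**What the plan says.** Protocol article, Drop-out criteria, gives three list items that run together in the text: "Refusal to participateDefault follow-upReported to be unsafe for treatment". The first two concern taking part and attending. The third concerns the treatment.

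Sample size builds in the loss: "We conservatively increase the sample size to 120, assuming 15% dropout rate". The base figure is stated as "A sample size of 100 will detect a significant difference using ANOVA with 80% power and 0.05 significance level".

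Adverse event handling deals with a closely related event, unusual conditions such as intolerable pain, in another way: "LMHFV treatment will be terminated and clinicians will follow-up the patient". Data collection, monitoring, and management speaks of withdrawal only for subjects who no longer wish to continue.

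Under Interventions, treatment starts 3 days after the operation and lasts 14 days, with follow-up to 6 months. Under Plain radiographs, films are taken at baseline and at 6, 12 and 26 weeks.

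**The concern.** Stopping a treatment and leaving a trial are different events. The Drop-out criteria section puts them in one list, so a site that follows it may end X-ray and functional visits for a patient whose only change is that the platform was judged unsafe. The sample size accepts this, since it counts drop-outs as lost.

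Losses of this kind happen after randomisation and may be linked to the treatment. Only one arm receives vibration. If vibration itself causes some of the intolerance, and if those patients heal more slowly than the rest, their loss would make the vibration arm look better than it is. Outcomes that were never collected cannot be recovered at the analysis stage.

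**Working it through.** **Inputs from the Protocol article.** Base 100, power 80%, level 0.05, dropout 15%, enrolled 120, and a 20% shorter healing time with no mean or SD (Sample size); two-sided testing (Statistics); treatment and X-ray times as above. **Assumed:** 1:1 allocation, 60 per arm, because the ratio is not stated.

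**1. The plan's own figure.** 100/(1 − 0.15) = 117.6, so 118, which agrees with a rounded 120. (100 × 1.15 = 115 fits less well.) After 15% loss, 120 × 0.85 = 102 remain and 18 are lost. The figure reproduces only if drop-outs contribute nothing to the powered comparison.

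**2. Timetable.** Counted in calendar days, treatment ends at about day 3 + 14 = 17. Counted as 14 sessions at five per week, it takes 14/5 = 2.8 weeks. The first post-baseline film is at 6 weeks, day 42. On either count, every patient in both arms is off treatment at every post-baseline film. A patient who stopped in the first week can supply the same films as one who finished.

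**3. The two sections side by side.** If the follow-up by clinicians under Adverse event handling means trial follow-up, it contradicts Drop-out criteria. If it means clinical care only, Drop-out criteria governs and the outcome is lost. Either reading needs a correction.

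**4. Scale for a bias.** The 100 cannot be derived without an SD. Solving backwards with 50 per arm: d = (1.960 + 0.842) × √(2/50) = 0.56 (0.57 with the t distribution). For a 20% effect this implies an SD of about 0.20/0.56 = 36% of the control mean.

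**5. Illustration of selective loss.** Assumptions not in the documents: no true effect; m patients lost, all from the vibration arm of 60; they heal k SD slower than those who remain. Then

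- bias b = (m/60) × k, in SD units;
- SE = √(1/(60 − m) + 1/60);
- type I error = P(Z > 1.96 − b/SE) + P(Z < −1.96 − b/SE).

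Example, m = 9 and k = 1: b = 0.15, SE = 0.190, b/SE = 0.788, type I error = 0.121 + 0.003 = 12.4%.

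| Lost (m) | Bias in SD, k = 0.5 to 1.0 | Type I error |
|---|---|---|
| 3 | 0.03 to 0.05 | 5.2% to 5.8% |
| 9 | 0.08 to 0.15 | 6.8% to 12.4% |
| 18 | 0.15 to 0.30 | 11.6% to 32% |

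The powered difference is about 0.57 SD. The last row puts the whole 15% allowance into one arm and one reason, so it is an extreme. Losses equal in number and kind in both arms give no such bias.

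**6. Power if those who stop are kept.** With the implied d, 120 analysed gives about 87% power against 81% with 102, before dilution. With 60 per arm, 80% power needs d = 2.80 × √(2/60) = 0.51, which is 0.51/0.56 = 91% of the planned effect. So if all 120 are followed, about 5 of the 60 vibration patients (60 × 0.087 = 5.2) could gain nothing at all before power falls below 80%.

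**The case against.** The other side has a good deal to say.

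- **No exclusion is stated.** A reader might infer that the analysed set is selected by response to vibration. The article does not support that. It names no analysis set and nowhere says that drop-outs are removed. A definition may sit in a document not shown, and its absence here is no fault. Nor does any drop-out criterion depend on healing; the relevant word is tolerance, not response. This stands.
- **Differential loss is not shown.** The sham group also stands on the platform soon after surgery, under the same criteria, and patients and investigators are blinded during treatment. Standing pain can arise in either arm. The article reports no known adverse events with the device, although the earlier trial it describes was in healthy, active, independent women. This stands: a difference between arms is possible, not established.
- **The 15% is not a safety figure.** It covers refusal, default and safety in both arms. Treating all of it as slow healers lost from the vibration arm is a worst case.
- **Some outcomes are protected.** Mortality comes from the hospital system, and adverse events during the study are documented. What is at risk is mainly the X-ray and functional data.
- **Envelope timing.** A reader might also infer that opening the envelope at consent, before the first session, adds to the bias. No consent date is given, the inclusion criteria suggest eligibility is settled after fixation, and a loss before any session cannot reflect tolerance of vibration. This is not part of the point.

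What remains is that the safety item is listed as a drop-out reason, the sample size treats drop-outs as lost, and another section handles a similar event differently.

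**Conclusion.** The point holds as a badly fixed criterion and an internal inconsistency. Followed as written, the Drop-out criteria section can cost the primary outcome in patients who only stopped a 14-day treatment, while Adverse event handling suggests that they are followed. The resulting risk is selection after randomisation related to tolerance of treatment. Any bias would favour vibration if such losses fall mainly in that arm and in slow healers, and neither condition is established.

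The size is unknown because the safety share of the 15% is not given. It is small if such losses are few or balanced: with 3 one-sided losses the type I error stays at 5.2–5.8%. With 9 it could reach 6.8–12.4%. These figures rest on 1:1 allocation, no true effect, and lost patients healing 0.5 to 1.0 SD slower. The change is still worth making, because it is cheap and lost films cannot be replaced.

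**What to change.** Replace the Drop-out criteria section with two definitions:

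- *Treatment discontinuation*: treatment reported unsafe, or the patient declines sessions.
- *Study withdrawal*: the patient withdraws from follow-up, or is lost to follow-up.

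State that everyone who discontinues treatment continues all scheduled X-ray, functional, fall and mortality assessments to the end of follow-up, and is analysed in the allocated arm. Align Adverse event handling with this, so that it is clear that follow-up there includes the trial assessments. Let the 15% allowance refer to study withdrawal only. The clinical rule for stopping treatment is unchanged.

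The cost is protocol wording; the visits are already scheduled. The downside is some dilution of the effect by patients who stopped. No larger sample is needed while such patients are few, as step 6 of the working shows.
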